## Abstract

**Background:**

Early identification of HCV is a critical health priority, especially now that treatment options are available to limit further transmission and provide cure before long-term sequelae develop. Emergency departments (EDs) are important clinical settings for HCV screening given that EDs serve many at-risk patients who do not access other forms of healthcare. In this article, we describe the rationale and design of The Determining Effective Testing in Emergency Departments and Care Coordination on Treatment Outcomes (DETECT) for Hepatitis C (Hep C) Screening Trial.

**Methods:**

The DETECT Hep C Screening Trial is a multi-center prospective pragmatic randomized two-arm parallel-group superiority trial to test the comparative effectiveness of nontargeted and targeted HCV screening in the ED with a primary hypothesis that nontargeted screening is superior to targeted screening when identifying newly diagnosed HCV. This trial will be performed in the EDs at Denver Health Medical Center (Denver, CO), Johns Hopkins Hospital (Baltimore, MD), and the University of Mississippi Medical Center (Jackson, MS), sites representing approximately 225,000 annual adult visits, and designed using the PRECIS-2 framework for pragmatic trials. When complete, we will have enrolled a minimum of 125,000 randomized patient visits and have performed 13,965 HCV tests. In Denver, the Screening Trial will serve as a conduit for a distinct randomized comparative effectiveness trial to evaluate linkage-to-HCV care strategies. All sites will further contribute to embedded observational studies to assess cost effectiveness, disparities, and social determinants of health in screening, linkage-to-care, and treatment for HCV.

**Discussion:**

When complete, The DETECT Hep C Screening Trial will represent the largest ED-based pragmatic clinical trial to date and all studies, in aggregate, will significantly inform how to best perform ED-based HCV screening.

**Trial registration:**

ClinicalTrials.gov ID: NCT04003454. Registered on 1 July 2019.

**Supplementary Information:**

The online version contains supplementary material available at 10.1186/s13063-022-06265-1.

## Introduction

Hepatitis C (HCV) is the most common blood-borne infection in the USA, and the burden of disease is substantial and increasing [1]. As of 2018, 2.5 million individuals were estimated to be living with HCV and > 50% remain undiagnosed [2, 3]. Well-tolerated, highly effective, direct-acting antivirals (DAAs) have revolutionized HCV treatment, dramatically reducing morbidity, mortality, and transmission, although significant work remains to improve the HCV care continuum (Fig. 1) [4–7].

**Fig. 1 Fig1:**
[figure not shown]
Natural progression of hepatitis C virus (HCV) infection (**A**) and the HCV care continuum (**B**)

Screening for HCV is the crucial initial step for intervening among patients with undiagnosed HCV [7, 8]. The Centers for Disease Control and Prevention (CDC) currently recommends HCV screening for all adults aged 18 years or older at least once in a lifetime and routine periodic screening for individuals with ongoing risk. Despite these recommendations, in many healthcare settings, screening for HCV is driven by risk [9, 10]. However, individuals commonly do not know they are at risk, clinicians may be too busy to perform risk assessments, or patients may be unwilling or unable to provide risk information [11]. Thus, support for the performance of non-risk-based (nontargeted) screening has grown, similar to what was seen with HIV screening [12–14].

Emergency departments (EDs) are important clinical settings for infectious diseases screening, including HCV, given that they serve as our society’s medical safety-net by, in part, filling the gap for those who do not have consistent access to healthcare [15–18]. Over 135 million ED visits occur annually and EDs serve substantial numbers of at-risk patients, providing ample opportunity to identify patients with undiagnosed HCV [19]. Nontargeted versus targeted HCV screening and different linkage-to-care approaches have not been studied in head-to-head fashions in EDs, thus the comparative effectiveness and yield of these strategies remains unknown.

The objectives of The Determining Effective Testing in Emergency Departments and Care Coordination on Treatment Outcomes (DETECT) for Hepatitis C (Hep C) studies are to (1) compare the effectiveness of two forms of HCV screening—nontargeted and targeted HCV screening (Screening Trial); (2) compare the effectiveness of two forms of referral to treatment for ED patients identified with HCV—linkage navigation plus clinician referral versus clinician referral only (Linkage-to-Care Trial); (3) measure and compare programmatic costs and project long-term clinical outcomes, costs, and cost effectiveness of ED-based HCV screening and linkage-to-care (Cost Evaluation); and (4) examine the effects of disparities and social determinants of health on linkage-to-care, treatment initiation, and treatment completion among patients identified with HCV in the ED (Disparities and Social Determinants of Health Evaluation). This article describes the rationale and design of the Screening Trial and is reported in accordance with the SPIRIT Statement for clinical trials [20, 21]. The primary hypothesis of the Screening Trial is that nontargeted HCV screening is significantly associated with increased identification of new HCV diagnoses when compared to targeted HCV screening. The full Protocol (Version 3.3, Date February 17, 2022) is provided in the Supplemental Appendix.

## Methods

The DETECT Hep C Screening Trial was designed using the PRECIS-2 framework for pragmatic clinical trials (Figure S1), has been registered in ClinicalTrials.gov, and will be reported in accordance with CONSORT guidelines [22, 23].

### Trial design

For this trial, we will perform a multi-center prospective pragmatic randomized two-arm parallel-group superiority trial, comparing two HCV screening strategies in the ED (Fig. 2). Allocation will be balanced using a 1:1 patient visit-level random allocation scheme built into the electronic health systems (EHSs) for each ED.

**Fig. 2 Fig2:**
[figure not shown]
Study schematic for The DETECT Hep C Trials, including the Emergency Department (ED) Screening Trial (**A**) and the ED Linkage-to-Care Trial (**B**). Abbreviations: HCV, hepatitis C; PWID, person who injects drugs

### Study setting

This trial will be performed in the EDs at Denver Health Medical Center (Denver, CO), Johns Hopkins Hospital (Baltimore, MD), and the University of Mississippi Medical Center (Jackson, MS) with a cumulative total of approximately 225,000 annual adult visits (Table 1). These sites were selected because of the heterogeneity of populations served. Each is geographically distinct and serves patient populations that are racially and ethnically diverse, underinsured, and have ongoing local HCV epidemics. Additionally, each ED has investigators that are experts in infectious diseases screening in EDs, which improves the likelihood of successful completion of this trial. Denver Health will serve as the coordinating site for this project.

**Table 1 Tab1:** Study site characteristics for The DETECT Hep C Emergency Department Screening Trial

Site	Setting	Hospital type	Annual ED census (visits)	Hispanic or non-White race^a^ (%)	Uninsured patients^b^ (%)	Birth cohort^c^ (%)	PWID (%)
Denver Health MC	Urban	L1/C/SN/T	96,000	53%	17%	30%	7%
Johns Hopkins Hospital	Urban	L1/U/T	69,000	77%	15%	31%	6%
University of Mississippi MC	Urban	L1/U/T	65,000	58%	28%	32%	Unknown

*Abbreviations: MC* Medical center, *ED* Emergency department, *L1* Level 1 trauma center, *C* County, *SN* Safety-net, *U* University, *T* Teaching/academic, *PWID* Person who injects drugs

^a^Asian, Black, Hispanic/Latin, American or Alaskan Native, Native Hawaiian, or Non-Hawaiian Pacific Islander

^b^Defined as uninsured or sponsored by a state healthcare discount program. Does not include Medicaid or Medicare

^c^Defined as birth years from 1945 to 1965

### Eligibility criteria

Consecutive ED patients ≥18 years of age will be eligible for inclusion if they are considered clinically stable by screening nurses or physicians and capable of providing consent for medical care. Due to the integrated, pragmatic nature of the study, patients will be enrolled 24 h per day, 7 days per week. Patients will be excluded if they (1) are <18 years of age; (2) are unable to consent for care (e.g., altered mentation, critical illness or injury); (3) have already been tested for HCV as part of the trial; (4) are identified as already living with HCV, either by self-report or through identification of a prior positive HCV result in the electronic medical record; or (5) have an anticipated ED length of stay <60 min.

### Interventions

This trial consists of a comparative evaluation of two HCV screening strategies, nontargeted and targeted screening. Patients who are allocated to nontargeted screening will be notified by the nurse that voluntary free rapid HCV testing will be performed during the ED visit unless declined (i.e., opt-out consent). Patients who are allocated to targeted screening will be presented with a brief risk assessment (Table 2). Those who have an affirmative response to any question will be considered at increased risk for HCV and notified by the nurse that voluntary free rapid HCV testing will be performed during the ED visit unless declined (Figure S3). Patients in the targeted arm who deny all risk will be considered low risk and HCV testing will not be offered.

**Table 2 Tab2:** Targeted risk assessment for HCV. Any affirmative response is considered at risk

1. Patient’s birth year between 1945 and 1965?	
2. Have you ever injected or snorted drugs?	
3. Do you have a tattoo or body piercing that you received in an unregulated setting?	
4. Have you ever had a blood transfusion or received an organ before July 1992?	

Adapted from the CDC, USPSTF, and AASLD-IDSA guidelines for HCV screening

Our brief risk assessment includes questions adapted from recommendations by the CDC, US Preventive Services Task Force (USPSTF), American Association for the Study of Liver Diseases (AASLD), and Infectious Diseases Society of America (IDSA). The questions ask if the patient was (1) born between 1945 and 1965, (2) ever injected or snorted drugs, (3) ever received a tattoo or piercing in an unregulated setting, or (4) received a blood transfusion or organ transplant before 1992 [9–11, 24]. Risk assessment will be incorporated into electronic medical screening and patient tracking systems in each ED. As such, nurses will use this tool while electronically entering responses to each of the risk questions during screening. Nurses will apply the set of risk questions to all patients who meet criteria for inclusion and are allocated to the targeted screening arm.

All HCV screening will be voluntary with consent for testing obtained in a verbal manner as part of clinical care and separate from consent for general emergency care. All processes will be fully integrated into usual emergency care with HCV antibody (Ab) test results returning during the ED visit. Central laboratory-based HCV Ab assays will be used at all institutions (Denver Health Medical Center: OraQuick Rapid HCV Antibody Test, OraSure Technologies, Bethlehem, PA; Johns Hopkins Hospital: Roche Elecsys® Anti-HCV II, Roche Diagnostics, Indianapolis, IN, and OraQuick Rapid HCV Antibody Test, OraSure Technologies, Bethlehem, PA (point-of-care samples); University of Mississippi Medical Center: ARCHITECT Anti-HCV assay, Abbott Laboratories, Abbott Park, IL), with subsequent HCV ribonucleic acid (RNA) assays for those who test Ab+.

### Allocation

#### Sequence generation, allocation concealment, and implementation

Participants who meet criteria for inclusion will be randomly assigned at the ED visit level in a 1:1 ratio to each study arm using simple randomization incorporated into the EHS (Epic, Epic Systems Corporation, Verona, WI) at each institution. Sequence generation will occur real-time in the background of the EHS using a computer-generated random number algorithm developed and validated at each site. Integration of randomization into the EHS will allow for real-time concealed allocation. As such, patients will be offered HCV testing based on the result of the screening arm to which they are assigned during triage of the ED visit. In the case of the targeted arm, the results of the risk assessment evaluation performed by the triage nurse will dictate HCV testing. All randomization and enrollment procedures will be completely integrated into EHS workflow at each site.

### Blinding

Nurses who perform screening and all other ED staff (e.g., physicians, technicians) will understand the conceptual goals of the trial but will be blinded to study hypotheses, and patients will be completely blinded to the purpose of the study.

### Recruitment

Given the pragmatic nature of the trial and the full integration of all study procedures, recruitment will occur 24 h per day, 7 days a week as part of actual ED care. As such, all patients who meet eligibility criteria will be included and randomized.

### Participant timeline

Primary research activities, including randomization, screening, testing, and referral to care for those who test positive for HCV antibodies (Abs), will occur during the patient’s ED visit. Longitudinal outcomes will be collected using structured retrospective chart review methods for those who test positive for HCV in the ED for a minimum of 6 months but up to 18 months from the time of diagnosis. There is no compensation for trial participation and all post-trial care will be usual care for patients.

### Outcomes

The *primary outcome* for this trial will be confirmed cases of newly diagnosed HCV, defined as patients who test positive for HCV Ab and HCV RNA. *Secondary outcomes* will include *all* patients identified with HCV in anticipation of testing those with previously diagnosed HCV (i.e., those who do not identify as having been previously diagnosed and who are re-diagnosed during this trial), as well as HCV test acceptance and completion, and progression through the HCV care continuum (i.e., receipt of RNA results, evaluation by a HCV treatment expert, treatment with DAAs, and sustained virologic response at 12 weeks after treatment completion [SVR12]).

### Sample size

#### Screening Trial—original sample size estimation

All sample size estimates for this trial were performed using Monte Carlo simulation in SAS Enterprise Guide Version 7.1 (SAS Institute, Inc., Cary, NC). Informed by medical literature, past experiences with HIV screening in EDs, and pilot data, we made the following assumptions: (a) nontargeted screening, 100% test offer, 60% test acceptance, 70% test completion, 5% Ab+ prevalence, and 65% RNA+ prevalence among those who test HCV Ab+ and (b) targeted screening, 33% test offer, 60% test acceptance, 70% test completion, 10% Ab+ prevalence, and 65% RNA+ prevalence among those who test HCV Ab+. The original sample size estimate was performed using series of 1000 simulated trials and a hypothesized effect of a 25% increase in the number of new HCV diagnoses (i.e., risk ratio [RR] = 1.25), resulting in a minimum of 50,000 visits across all sites to achieve a power >80% (*α* = 0.05). This was estimated to result in 13,965 completed HCV tests and 611 confirmed newly diagnosed patients (Fig. 3).

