### Statistical methods

After cleaning and locking the dataset, the primary analysis will be performed using the intention-to-treat principle while blinded to allocation. Continuous data will be reported as medians with interquartile ranges (IQRs) and categorical data as counts, proportions, and/or percentages with 95% confidence intervals (CIs). Bivariate statistical tests (e.g., Wilcoxon rank-sum test, Fisher’s exact test, etc.) will be used to compare variables between study groups. Patient-level data will be reported for all patient-level variables (e.g., age, sex/gender, race, ethnicity), although the primary unit of analysis will be patient visits. No interim analyses are planned given the pragmatic trial approach and minimal risk to subjects. Given the randomized design, the primary comparison will include an unadjusted RR for newly-identified HCV patients (primary outcome) with 95% CIs, specifically comparing nontargeted HCV screening to targeted HCV screening (primary hypothesis), while using a random effect hierarchical model to account for institution-level clustering, if present [26–28]. Sensitivity analyses will be performed to account for patients who were identified as Ab+ but RNA-, and subsequently determined to have been previously treated for HCV. Secondary comparisons will include all other outcomes by study arm, stratified by age, sex/gender, race, ethnicity, and institution. Statistical significance for the primary analysis will be defined as *p* <0.05 based on two-tailed statistical testing, which includes a lower 95% confidence limit of the RR >1.0. Although we do not anticipate significant missing data, multiple imputation will be used in instances where variables have >5% missingness. Although no formal interim analyses are planned for this trial, the study team may perform preliminary analyses for purposes of presentation at scientific meetings; these instances, if they occur, will be explicitly qualified as such and described as preliminary.

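### The listed inputs to the original sample size give 566 diagnoses, a risk ratio of 1.52 and about 99.8% power, and do not fit the stated 611 diagnoses, risk ratio of 1.25 and 50,000-visit minimum

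*Protocol article*

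**What the plan says.** The section on the original sample size estimation gives these inputs:

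- Nontargeted arm: 100% offer, 60% acceptance, 70% completion, 5% Ab+, and 65% RNA+ among the Ab+.
- Targeted arm: "targeted screening, 33% test offer, 60% test acceptance, 70% test completion, 10% Ab+ prevalence", with the same 65% RNA+ among the Ab+.

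The planning effect is "a hypothesized effect of a 25% increase in the number of new HCV diagnoses", given as RR = 1.25. The result is reported as "resulting in a minimum of 50,000 visits across all sites to achieve a power >80" per cent at α = 0.05, and then: "This was estimated to result in 13,965 completed HCV tests and 611 confirmed newly diagnosed patients".

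Table 3 repeats 5% and 10% Ab+, and 65% RNA+ in both arms, as the original assumptions. The section on the blinded re-estimation again names 1.25 as the original hypothesised RR. Allocation is 1:1 (Trial design). Significance is "defined as *p* <0.05 based on two-tailed statistical testing" (Statistical methods).

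**The concern.** The cascade inputs fix the expected number of diagnoses in each arm, and so the expected total and RR. The section then states a total and an RR of its own, and the two sets differ.

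This paragraph is the published basis for the trial's size. Table 3 also uses its inputs as the baseline for judging observed performance. The re-estimation reports that RRs of 1.35 (weighted) and 1.45 (inverse probability weighted) would be needed for more than 80% power. An RR of 1.52, which the printed inputs imply, lies above both thresholds; the stated 1.25 lies below both. As printed, the calculation cannot be replicated, and the Ab+ and RNA+ baselines in Table 3 cannot both be relied on.

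**Working it through.** **Inputs.** 50,000 visits at 1:1 give 25,000 per arm. The cascade percentages are those of the original sample size estimation. The test is two-sided at 5%, and the unit of analysis is the visit.

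**Tests (the plan's own figure).**
- Nontargeted: 25,000 × 1.00 × 0.60 × 0.70 = 10,500
- Targeted: 25,000 × 0.33 × 0.60 × 0.70 = 3,465
- Total: 13,965, exactly as stated. The offer, acceptance and completion inputs are therefore consistent with the printed result.

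**Diagnoses.**
- Nontargeted: 10,500 × 0.05 × 0.65 = 341.25
- Targeted: 3,465 × 0.10 × 0.65 = 225.2
- Total: 566.5 against the stated 611, a shortfall of 44.5/611 = 7.3%.

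**RR.** Acceptance, completion and RNA+ are equal in the two arms and cancel, so RR = (1.00 × 5%)/(0.33 × 10%) = 1.515. Neither rounding nor the choice of test turns this into 1.25.

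**Power under the printed inputs.** The per-visit risks are p₁ = 341.25/25,000 = 0.01365 and p₂ = 225.2/25,000 = 0.00901, a difference of 0.00464. The standard error is √{[p₁(1−p₁) + p₂(1−p₂)]/25,000} = 0.000946, so z = 0.00464/0.000946 − 1.96 ≈ 2.94 and power is about 99.8%. A simulation of 20,000 trials, using the rule that the lower 95% limit of the RR exceeds 1, also gave 99.8%. The same normal approximation needs 8,163 visits per arm for 80% power, about 16,300 in total (about 17,200 with continuity correction). So 50,000 is not the minimum under these inputs.

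**What would give 611 with 13,965 tests?** With the nontargeted arm as printed, the targeted arm must supply 611 − 341.25 = 269.75 diagnoses from 3,465 tests. That is a yield of 7.8% per test, against the printed 10% × 65% = 6.5%. Two single-input changes do this:
- Targeted Ab+ 12%: 3,465 × 0.12 × 0.65 = 270.3
- Targeted RNA+ 78%: 3,465 × 0.10 × 0.78 = 270.3

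Both give 611.5 diagnoses, RR 341.25/270.3 = 1.263 and power of about 82% (simulation 82.6%).

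Other single changes fail:

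| Change | Diagnoses | RR | Tests |
|---|---|---|---|
| Targeted offer 39.6% | 611.5 | 1.26 | 14,658 |
| Nontargeted Ab+ 5.65% | 610.8 | 1.71 | 13,965 |
| RNA+ about 70% in both arms | 611 | 1.515 | 13,965 |
| Nontargeted Ab+ 4.125% | 507 | 1.25 | 13,965 |

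**At exactly RR 1.25, nontargeted arm fixed.** 341.25/1.25 = 273 targeted diagnoses, 614 in total, and about 79% power.

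**The case against.** The strongest reply is that RR 1.25 is a planning effect set separately from the cascade, and that 99.8% literally satisfies a power above 80%. The second part is true as far as it goes, since the article does not say the power was only just above 80%. But it calls 50,000 visits the minimum for that power, and about 16,300 would suffice under the printed inputs. The first part does not rescue the figures. Imposing 1.25 from the nontargeted arm replaces the printed targeted yield and gives 614 diagnoses; imposing it from the targeted arm gives 507. Neither is 611 from the printed inputs.

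It can also be said that little now turns on this calculation, and much of that stands. The 13,965-test target carried forward does not depend on Ab+ or RNA+ prevalence. Enrolment has already passed 50,000 visits. The re-estimated powers at RR 1.25 (65.7% weighted, 42.9% inverse probability weighted) use observed offer, acceptance, completion and aggregate prevalence. The intended effect is not in doubt either, because 1.25 is named in both sample size sections.

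A reader might infer that targeted Ab+ was really 12% and that the 10% is a misprint. That fits well, but targeted RNA+ of 78% fits identically because only the product matters. Fig. 3 and the full protocol, which might settle it, are not shown.

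**Conclusion.** The stated figures are mutually inconsistent. The printed inputs give 566 diagnoses where 611 is stated, RR 1.52 where 1.25 is stated, and about 99.8% power at a number of visits described as the minimum for more than 80%. The diagnosis count and RR follow by multiplication alone. The power figures rest on a two-sided 5% comparison of per-visit risks with no inflation for site clustering, in line with the article's decision not to inflate.

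The likely explanation is that a printed targeted-arm input differs from the one simulated; the article does not identify which.

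A reader might also infer that the trial was wrongly sized from the start. The documents do not support this. With a targeted yield of about 7.8% per test, 50,000 visits give about 82% power. At exactly RR 1.25 the power is about 79%, and the gap to 80% is within the simulation error of 1,000 trials: √(0.79 × 0.21/1,000) ≈ 1.3 percentage points. The fault is a misstated assumption or misstated results. It is not a demonstrated shortfall in the original design.

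**What to change.** Go back to the inputs of the original SAS simulation and establish which targeted-arm values were used. Then correct the original sample size estimation and the original-assumption columns of Table 3 together, so that inputs, RR, diagnoses, minimum visits and power agree with one another and with the RR of 1.25 that the re-estimation section calls the original hypothesised effect. If the simulated RR was about 1.26 and was rounded, say so, because exactly 1.25 goes with 614 diagnoses and about 79% power. The replacement value should come from the simulation record; working backwards from 611 cannot distinguish a changed Ab+ from a changed RNA+.

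The cost is a check of archived code, possibly one rerun, and a few corrected figures. It needs no extra patients and no change to the test target, the re-estimated powers or the analysis.
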